## Abstract

**Background:**

Ankle osteoarthritis (OA) is a serious problem with high associated pain and disability. While education and exercise are recommended for the initial management of OA, this has not been investigated in ankle OA. The primary aim of this study is to establish the feasibility of running a full-scale randomised controlled trial (RCT) investigating a combined education and exercise program compared to a general advice program for people with ankle OA. The secondary aims are to collect preliminary data which will inform sample size calculations, and understand the perspectives of people with ankle OA on their participation in the trial.

**Methods:**

Thirty individuals aged 35 years or older with symptomatic radiographic ankle OA will be recruited from the community and randomised to receive either a combined education and exercise program or a general advice program, both of which will be delivered by a physiotherapist in a group setting. Primary outcomes of feasibility include responses to study advertisements, number of eligible participants, recruitment rate, adherence with the intervention, fidelity of the intervention, adverse events, drop-out rate, and credibility and expectancy of the intervention. Secondary participant-reported outcomes will include global rating of change, patient acceptable symptom state, severity of ankle pain and stiffness, self-reported function, quality of life, satisfaction with treatment, and use of co-interventions. Follow up will be at 8 weeks and 3 months. Physical measures of 40 m walking speed, timed stairs descent, heel raise endurance and ankle dorsiflexion range of motion will be collected at baseline and 8 weeks. Primary feasibility outcomes will be reported descriptively, and estimates of the variability of secondary participant-reported and physical outcomes will be calculated. Semi-structured interviews will be conducted with participants to understand perspectives about the intervention and participation in the trial, with data analyzed thematically.

**Discussion:**

Study findings will establish the feasibility of running a full-scale RCT to investigate a combined education and exercise program compared to a general advice program for people with ankle OA. This study is a necessary first step to advance the international research agenda of evaluating the efficacy of exercise in the management of ankle OA.

**Trial registration:**

ACTRN12623000017628. Registered 10 January 2023, https://www.anzctr.org.au/ACTRN12623000017628.aspx.

**Supplementary Information:**

The online version contains supplementary material available at 10.1186/s13047-023-00669-1.

## Background

Ankle osteoarthritis (OA) is estimated to affect between 3.4% [1] and 6.5% [2] of the adult population and is a known long-term consequence of ankle sprains and fractures, which are among the most common injuries sustained in general and sporting populations [3]. Due to the post-traumatic nature, ankle OA affects individuals in their third decade of life [3]. People with ankle OA report “*crippling*” and “*limiting*” pain, which affects basic ambulation, participation in recreational activities, and work [4]. Quantitative research confirms these findings, with evidence of high levels of pain and disability, and low quality of life (QoL) [5]. Disability and QoL in ankle OA are similar to that reported by individuals with end-stage renal disease, radiculopathy and congestive heart failure [6].

There is little robust evidence to guide the management of ankle OA. A 2015 systematic review did not identify any evidence-based non-surgical interventions for ankle OA [7], and surgical management is prone to complications. It is estimated that 42% of ankle joint replacement surgeries require surgical revision [8], and 63% of patients experience adverse events [9]. With poor outcomes following surgery and the recognition that surgical management should be reserved for those who fail to respond to appropriate non-surgical management, there is an urgent need for effective, evidence-based non-surgical management for ankle OA.

Unlike hip and knee OA, there are no current clinical practice guidelines or recommendations for the management of ankle OA. Evidence-based guidelines for the management of hip and knee OA from the Osteoarthritis Research Society International (OARSI) state that all individuals should receive education about self-management and undertake regular aerobic and strengthening exercises [10]. The 2018 Royal Australian College of General Practitioners (RACGP) guidelines for the management of hip and knee OA recommend exercise and weight management as the first-line treatment [11]. Similarities in disease and reported impairments in pain, physical and emotional function in ankle [12, 13], knee [14] and hip [15, 16] OA suggest that similar approaches may be effective in managing these conditions. Physiotherapist-led exercise and education programs are associated with improvements in pain, function, QoL, physical activity, medication use, sick leave, and health care costs in people with hip and knee OA [17, 18]. However, the efficacy of such a program in ankle OA has not been investigated, and it is important not to extrapolate findings at the hip and knee to the ankle.

The primary aim of this study is to establish the feasibility of running a full-scale randomised controlled trial (RCT) investigating a combined education and exercise program compared to a general advice program for people with ankle OA. The secondary aims are to collect preliminary data to inform sample size calculations for a well-powered RCT, and understand the perspectives of people with ankle OA on their participation in the trial.

## Methods

### Study design

This feasibility study uses a mixed-methods approach with a central randomised parallel-group design and qualitative semi-structured interviews at trial completion. It follows the Standard Protocol Items: Recommendations for Interventional Trials (SPIRIT) guidelines [19], the CONSORT extension for randomised pilot and feasibility trials [20] and the Consensus on Exercise Reporting Template (CERT) [21]. Methodology and reporting of the semi-structured interviews will be guided by the Consolidated Criteria for Reporting Qualitative Studies (COREQ) [22]. The study is registered on the Australia New Zealand Clinical Trials Registry (ANZCTR; registration #: ACTRN12623000017628, registration date: 10 January 2023). Ethical approval has been obtained from The University of Queensland Human Research Ethics Committee (Approval #: 2018/HE002196) and all participants will provide informed consent prior to study participation.

### Participants

Individuals will be recruited using a broad recruitment strategy that has been successfully used in previous ankle OA research [13]. We will use paid and unpaid advertisements on social media (e.g., Facebook, Twitter), websites (e.g., Weekend Notes, Arthritis Australia, Arthritis Queensland), newsletters (e.g., UQ Update), radio (e.g., 4BC), and electronic and physical noticeboards in the greater Brisbane area. Posters will be given to physiotherapy and inter-professional health clinics to post in their practices. Advertisements will use simple language and include a range of images to appeal to diverse individuals.

Formal sample size calculations are not applicable for feasibility studies. We chose a sample of 30 participants for feasibility of recruitment within the 1-year study period, while allowing observation of sample variability and any adverse responses. Individuals with ankle OA will be required to meet the following eligibility criteria for inclusion: (i) aged over 35 years; (ii) ankle joint pain on most days for the last three months; (iii) severity of ankle pain in the last week ≥ 3 out of 10 on an 11-point numerical rating scale (NRS) anchored with ‘no pain’ at 0 and ‘worst pain imaginable’ at 10; (iv) modified Kellgren & Lawrence scale (K&L) OA grade ≥ 2 at the subtalar and/or talocrural joints defined as the presence of osteophytes and/or joint space narrowing [23]; (v) committed to undergo the allocated treatment and undertake all follow up outcome measurements; and (vi) able to understand verbal and written English. Study exclusion criteria are: (i) health problems or pain elsewhere that are more concerning than that at the ankle; (ii) received exercise and/or education-based treatment for ankle OA in the last three months; (iii) previous ankle arthrodesis or total ankle replacement on the affected ankle; (iv) neurological, vestibular or systemic arthritic conditions; (v) receiving treatment for cancer; and (vi) inability to undertake radiographic evaluations (e.g. pregnancy) and/or participate in the treatment program.

### Study procedures

The flow of participants through the study is shown in Fig. 1. Individuals who express interest in participating in the trial will complete a multi-stage screening process. First, they will complete a preliminary online screening survey and verbal phone screen to check eligibility. Second, individuals will undertake a comprehensive in-person physical examination by a registered physiotherapist to ensure that the individual’s ankle pain is arising from the ankle joint and not surrounding structures. Finally, individuals will undergo lateral and mortise view ankle x-rays at a radiology clinic to determine the presence of radiographic ankle OA at the subtalar and/or talocrural joints. Radiographs will be assessed by a researcher with radiology training to determine the stage of OA [23]. Interrater reliability of grading radiographic ankle OA severity in previous research from our group is substantial (Kappa: 0.69 (95% confidence intervals: 0.59, 0.79) [13]. Individuals who meet all eligibility criteria will complete informed consent documentation and baseline data collection with a research team member blinded to group allocation.

### Interventions

Trial interventions will be delivered by private practice physiotherapists who are registered with the Australian Health Practitioner Regulatory Agency and have at least five years of clinical experience and post-graduate physiotherapy qualifications. To ensure consistency in the delivery of interventions, trial physiotherapists will attend a training session on the trial methods and intervention protocols. Study interventions will be offered at two private practice physiotherapy clinics in different areas of Brisbane. Participants will select the physiotherapy clinic that is most convenient for them to attend.

#### Education and exercise intervention

The combined education and exercise intervention will be delivered in a supervised class format with 2–4 participants per class. Consistent with OARSI guidelines [10], participants will be provided education about OA, diagnosis and symptoms, international guidelines and evidence-based management. This information will be delivered in two group education sessions in the first week (week 1) of the intervention. The education session will be facilitated by a PowerPoint presentation and will contain ample opportunity for discussion and questions. Participants will be provided a handout of the PowerPoint presentation.

The exercise sessions follow resistance training guidelines from the American College of Sports Medicine [24]. There will be two group exercise sessions per week over six weeks (a total of 12 exercise sessions, each of 1-hour duration) delivered by a trial physiotherapist (weeks 2–7 of the intervention). There will be 2–3 days of rest between exercise sessions. The exercise program will include aerobic exercise (i.e., stationary bike), exercises for foot/ankle muscle strength (i.e., resistance band and body weight exercises), compound lower limb exercises (i.e., step ups), postural control/balance training (i.e., standing on compliant surfaces) and gentle stretching (Table 1). Strengthening exercise sessions will be prescribed as two sets of 10–12 repetitions and 1 min rest between sets. Load (Theraband® and free weight resistance) will be individualised to study participants and will be an intensity that the participants can perform between a maximum of 10 and 12 repetitions with correct form/technique and a patient-acceptable level of pain (determined dichotomously with the question ‘Are your current symptoms acceptable, when you take your general functioning and your current pain into consideration?’). If the participant cannot perform 10 repetitions with correct technique or acceptable pain, a lighter load/resistance will be used. If the participant can perform more than 12 repetitions with good technique and acceptable pain, then a heavier load/resistance will be used. The load/resistance will be individually evaluated by the physiotherapist for each exercise and load will be progressed to maintain this workload. Each exercise repetition will consist of a 2-second concentric phase, 1-second isometric hold, and 2-second eccentric phase with a 1-second rest between repetitions. Each set will take about 60–70 s to complete with a total time under tension of 50–60 s per set (and 100–120 s per exercise). Exercises done unilaterally will be performed on both legs, with one set of the exercise performed on the unaffected side. If time does not allow performance of all exercises bilaterally, the resisted foot and ankle exercises will be omitted on the unaffected side. The detailed exercise program, including prescription and progressions, is outlined in Supplementary file 1.

**Table 1 Tab1:** The components of the exercise program

**Warm up/ Aerobic exercise**	10 min of cycling on a cycle ergometer at a workload of ‘somewhat hard’ on the rate of perceived exertion (RPE) scale [25].
**Foot and ankle specific muscle strength (5 exercises)**	Five exercises for foot and ankle-specific muscle strength using body weight resistance or Theraband® resistance. The specific exercises are: calf raises (body weight resistance) and Theraband® resisted ankle dorsiflexion, ankle inversion, ankle eversion, and toe flexion.
**Compound lower limb muscle exercises (3 exercises)**	Three compound lower limb muscle strength exercises which include step up/downs (body weight resistance), squats/resisted knee extension (body weight or Theraband® resisted), and a pelvic lift/supine bridge (body weight resistance).
**Balance training (1 exercise)**	A standing balance exercise series with adjustment to base of support and addition of perturbations.
**Cool down**	Walking forward and backwards for 2–3 min at a self-determined comfortable pace, followed by gentle stretching of the ankle plantarflexors, quadriceps and hamstrings. Stretches are held for 30 s each.

Physiotherapists will record attendance; intensity (e.g., Theraband® colour or kilogram load), repetitions and sets for each exercise; patient-acceptable level of pain (acceptable vs. not acceptable); and any adverse events for each exercise session. If participants report an unacceptable level of symptoms following the previous exercise session, load will be carefully monitored and adjusted as needed.

Participants will not be given a home exercise program during the six weeks of group exercise classes. At the completion of the 6-week program, participants will be instructed to continue with the exercises twice a week at home (i.e., a home exercise program). A handout will be provided with instructions on how to complete each exercise, and when and how to progress.

#### General advice intervention

Participants allocated to the general advice group will attend one 1-hour group session, where they will receive general information about OA (e.g., the importance of keeping active and tips on managing symptoms) based on online resources from Musculoskeletal Australia (*Understanding Osteoarthritis*) [26] and Arthritis Australia (*Information Sheet on Physical Activity*) [27]. They will be provided with the online resources in advance of their group session. The group session will be guided by a PowerPoint presentation to facilitate discussion about the information in the resources, and ample opportunity will be provided for participants to ask questions. Participants will receive a half-page handout of tips reinforcing the advice provided in the presentation and the contact details for the physiotherapist. No manual treatment or exercise prescription will be provided. Physiotherapists will record attendance at the general advice session. This is a similar treatment to other RCTs on musculoskeletal conditions and has been found to be acceptable to participants (based on recruitment rates, retention and participant feedback) [28].

#### Concurrent treatments

Participants will be requested to refrain from seeking other treatments during the trial, and report any interventions used. If participants use regular medication (e.g., analgesic and anti-inflammatory drugs), orthoses, prescribed footwear or assistive devices (e.g., walking aids) on entry to the study, they will be permitted to continue with their use.

### Outcome assessment

Baseline participant demographic (e.g., sex, weight, height) and ankle OA (e.g., affected ankle, aggravating activities, and modified Kellgren & Lawrence scale (K&L) OA grade [23]) data will be collected. Participant-reported outcome measures will be collected at baseline, 8 weeks and 3 months post-commencement of the intervention using an online survey platform (Qualtrics). Follow up data will be collected on all participants, including those who deviate from or discontinue their treatment allocation.

Participants will complete weekly diaries throughout the 3-month study period to record any adverse events in relation to their ankle or general health, any treatment they sought and any changes to medication they take for their ankle. Diaries will be given to participants at their first treatment session, with instructions to email a photo of the diary to their physiotherapist weekly (or to return it at the exercise session for those in the combined education and exercise intervention). Participants will receive a weekly reminder from their physiotherapist to submit the diary. Use of interventions outside of the study will be recorded as type (e.g., medication use, physiotherapy), number and percentage.

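### Weekly diaries on adverse events and outside treatment go to the unblinded treating physiotherapist, and adverse events are collected by different routes in the two arms

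*Protocol article*

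**What the plan says.** Outcome assessment sets up the diary for all participants: "Participants will complete weekly diaries throughout the 3-month study period to record any adverse events in relation to their ankle or general health". It also covers "any treatment they sought and any changes to medication they take for their ankle". Diaries are handed out at the first treatment session, "with instructions to email a photo of the diary to their physiotherapist weekly". The exercise arm has an alternative: "or to return it at the exercise session for those in the combined education and exercise intervention". The prompt comes from the same person: "Participants will receive a weekly reminder from their physiotherapist to submit the diary".

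Four other places bear on this:

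- **Concurrent treatments:** "Participants will be requested to refrain from seeking other treatments during the trial". The same sentence asks them to report whatever they do use.
- **Study procedures:** neither participants nor treating physiotherapists can be blinded.
- **Education and exercise intervention, and Primary outcomes:** the physiotherapist records adverse events at every exercise session. The adverse-event outcome combines this record with the diaries.
- **General advice intervention:** "Participants allocated to the general advice group will attend one 1-hour group session". Attendance is the only thing the physiotherapist is said to record there.

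**The concern.** There are two linked problems.

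**The recipient.** A participant who sought other treatment, or who reacted badly to the program, has to tell the clinician delivering that program. Some may tone down or skip such an entry. The issue is sharper for those who stop treatment: the same section follows them up, so as written they would go on reporting to the physiotherapist whose program they left. Elsewhere the protocol takes care over independence. Fidelity is observed, and exit interviews are held, by people outside intervention delivery. The diary is an exception.

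**The difference between arms.** Adverse events have two planned sources in the exercise arm and one in the advice arm, and the way the diary is returned also differs. If pooled counts are set side by side, a difference between arms could reflect how events were collected as well as how many occurred.

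Adverse events are a listed primary feasibility outcome, and the abstract names co-intervention use as a secondary outcome. The study is a rehearsal for a full trial, so a collection route accepted here is likely to be carried forward.

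**Working it through.** The protocol gives no figure on this point to reproduce. The check is a count of planned collection occasions, followed by a comparison of the two arms.

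**Inputs**
- Diary: weekly for 3 months, both arms (Outcome assessment).
- Exercise arm: 2 education sessions in week 1, then 2 exercise sessions a week for 6 weeks, in weeks 2 to 7 (Education and exercise intervention).
- Advice arm: 1 session (General advice intervention).
- Session-based adverse-event record: each exercise session (Primary outcomes).

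**Step 1: number of diaries and reminders.** Weeks in 3 months = 3 × 365.25 / 12 / 7 = 13.04. This gives 12 to 13 weekly diaries, and as many reminders, depending on whether 3 months is read as 12 or 13 weeks and whether the last week is prompted. The number is the same in both arms.

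**Step 2: planned adverse-event recording occasions per participant**

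| Source | Exercise arm | Advice arm |
|---|---|---|
| Weekly diary | 12–13 | 12–13 |
| Physiotherapist record at exercise sessions | 6 × 2 = 12 | 0 |
| Total | 24–25 | 12–13 |

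The ratio of exercise to advice is 24/12 = 2.0 or 25/13 = 1.9. The 12 session records assume full attendance, so the exercise total is a maximum. An event noted at a session may also appear in the diary, so this is a ratio of occasions to record and does not predict a ratio of events.

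**Step 3: return route for the diary.** In weeks 2 to 7 the exercise arm has 12 chances to hand the diary over in person and the advice arm has none. Outside those 6 weeks both arms email a photo.

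**Step 4: by outcome.** For adverse events, both the number of sources and the return route differ by arm. For co-interventions, the diary serves both arms and only the return route differs. In both arms the recipient is the treating physiotherapist.

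**Step 5: link to the progression decision.** The Table 2 criteria are consent rate, adherence, fidelity and completion of participant-reported outcomes at 3 months. None draws on the diary.

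**The case against.** The strongest reply has five parts.

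1. **Under-reporting is not shown.** The protocol has no data on it, and weekly diaries with weekly prompts favour fuller reporting. Participants are also told to report any intervention used, and may continue regular medication, orthoses, prescribed footwear and assistive devices. This stands: the effect is a plausible risk whose direction is open.
2. **Little rests on the counts.** The analysis is descriptive and no Table 2 criterion uses them. This stands, and it keeps the point minor. A descriptive table by arm would still be read as a comparison.
3. **There may be a second route for co-interventions.** The abstract lists their use among participant-reported outcomes followed up at 8 weeks and 3 months, and those outcomes are collected online. Secondary outcomes describes no such item, so this is possible but not stated. Exit interviews might also reveal discomfort with the diary.
4. **The difference in return route is limited.** Handing in is optional and confined to weeks 2 to 7. This stands for the route, but it does not remove the additional session-based adverse-event record.
5. **Direct receipt lets the treating clinician see adverse events.** This is a real advantage, and any change must preserve it by forwarding.

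A reader might also infer that the reminders give a one-session comparator about 13 extra therapist contacts and so change it. The protocol does not support that. The 12 to 13 reminders go to both arms, and their form and content are not stated, so a one-line message would fit the wording. The Discussion says the group format is meant to provide patient-therapist interaction in both interventions, and advice participants already receive "the contact details for the physiotherapist".

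**Conclusion.** The point holds as a minor weakness of design. As written, adverse events are not collected alike in the two arms: up to 24 to 25 planned recording occasions per participant against 12 to 13, with the diary the only stated ongoing source for the advice arm. Diaries on adverse events and outside treatment go to the unblinded treating physiotherapist, with an in-person return option in one arm only.

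The conclusion assumes full attendance at the 12 exercise sessions and that the article describes every collection route. How far reporting is affected, in which direction, and whether by different amounts in each arm cannot be derived from the protocol. A reader should not conclude that events or outside treatments will be under-reported, that the comparator is contaminated, or that the decision to proceed is at risk.

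**What to change.** Collect the weekly diary in both arms as a short form on Qualtrics, which already carries the participant-reported outcomes. Have reminders sent automatically or by study staff outside treatment delivery. Forward adverse-event reports promptly to the physiotherapist, and offer paper to anyone who needs it.

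Keep the physiotherapist's session record. Report diary-sourced adverse events by arm in one table and session-recorded events in the exercise arm in another, and base any between-arm description on the diary data.

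The cost is setting up one survey form, a forwarding step for adverse events and provision for paper. Physiotherapists save the time now spent on reminders and diary receipt, and the separate tabulation adds almost nothing.
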